#### Standard care

Standard care is known to be quite heterogeneous. Family meetings are offered in all participating sites but the frequency and method of conduct varies; thus we are mindful that some control participants will receive a family meeting, although these are typically not formally structured. Our research has been designed in recognition of this and we will also collect data on the frequency of family meetings conducted in the control group.

#### Intervention

The intervention which is administered according to clinical guidelines for conducting family meetings is comprehensively outlined in the earlier work of [name] and colleagues [32]. In summary, the guidelines incorporate: (1) principles for conducting family meetings; (2) pre-meeting procedures such as liaising with the patient/family and prioritising issues; (3) deciding who needs to attend the family meeting; (4) a procedure for conducting the meeting; and (5) strategies for follow up after the meeting, including data on whether or not the priority issues for the family carer have been addressed. The meetings are intended to take no longer than one hour.

Approximately four facilitators will be appointed at each of the participating sites to convene and conduct the family meeting/intervention. The facilitators will be nurses, doctors, social workers or psychologists with extensive clinical palliative care experience and relevant academic qualifications. Facilitators will be identified by the director of palliative care at each of the participating sites. They will receive training in administering the intervention which will incorporate conducting the family meeting according to the aforementioned guidelines; along with communications skills theory and practicum. In order to limit variation of intervention delivery at each site the training approach for all facilitators will be consistent and will be conducted face to face over the course of 1 day.

#### Data collection

Eligibility data will be recorded along with reasons for refusal to participate (for those eligible who are willing to provide this information). Data collection will involve mixed methods including quantitative and qualitative data.

##### Family carer measures

We have administered similar quantity and type of measures to family caregivers with no negative sequelae apparent [33].The 12 item version of General Health Questionnaire (GHQ) [34]. The GHQ has demonstrated good reliability and validity and is commonly used as a screening tool to detect those likely to develop psychiatric disorders. It is a measure of the common mental health problems including the domains of depression, anxiety, somatic symptoms and social withdrawal [35, 36]. The GHQ is scored on a Likert scale, with a maximum score of 36; score ≥15 indicates evidence of distress; and score >20 suggests severe problems and psychological distress. Family carers who meet the cut off for profound psychological distress (>20) at T1 will be advised of such and recommended that they seek formal medical/psychological review from their treating doctor or palliative care team. They will however still be eligible to participate in the study. GHQ will be administered at all three time points.The Family Inventory of Needs (FIN) [37] has 20 items and has been shown to have good reliability and validity [37, 38] . Administered at times 1 and 2 only as this focuses on caregiving while the patient is alive.The Preparedness for Caregiving Scale (PCS) [39] has 8 items and has been shown to have good reliability and validity [38] . Administered at times 1 and 2 only as this measure focuses on caregiving while the patient is alive.The Short form health survey version 2 (SF12-v2) is 12 items quality of life measure that has been widely used across many diverse populations. It is a measure of both physical and emotional quality of life [40]. Administered at all three time points.The Caregiver Quality of Life Index-Cancer (CQOLC) scale is a measure of caregiver quality of life. The scale has been found to be a reliable and valid measure of quality of life for caregivers of cancer patients and cancer patients receiving palliative care [41]. As the questions do not specifically relate to cancer, they are appropriate for caregivers of non-cancer palliative care patients. Administered at times 1 and 2 only as this measure focuses on caregiving QOL while the patient is alive.Family carers will also complete a socio-demographic survey including details and level of function of their relative via the Australian Karnofsky scale [42]. Administered at T1 only.At time 3 (after death) the family carer will also complete a measure of the quality of the death which will be measured using a shortened version of the Quality of Death and Dying Questionnaire [43, 44]. This measure has been widely used with similar populations and includes 17 items that measure different aspects of the dying experience.

We will also collect data on the date of patients’ death to assist with determining the impact of having the family meeting further away from death.

##### File audit (Patient record)

For the second hypothesis (H2), data will be collected from the patients’ medical records using a File Audit Checklist and also from data from the hospital administrative data sets (which include ICD-10-AM codes which are collected for the Department of Health). These data will include indicators of quality end-of-life care [45]: hospital admissions and length of stay, ED presentations, hours in ICU, chemotherapy administration in the last 30 and 14 days of life, a new regimen of chemotherapy in last 30 days of life, and place of death. Data will also be collected on access to supportive care services, evidence of advanced care plans, and attendance at family meetings.

#### Sample size, power calculation and feasibility

The primary outcome for H1 is measured via the GHQ, a 12-item scale with a possible range of 0-36. Our previous study [46] of 275 family carers in which the mean GHQ difference was 2.8 (SD = 5.6), represents a medium effect size (ES) of 0.5 which is a common estimate of a minimal important difference [47]. The sample size calculations are based on a smaller mean difference between groups of 2.4, as some carers in the control group will have family meetings as part of standard care. Estimated sample size for two-sample comparison of means Test Ho: m1 = m2, where m1 is the mean in population 1and m2 is the mean in population 2 is 97 per group (total *n* = 194). This calculation assumes that alpha = .05 (two sided), power = .90 (90 %), m1 = 16.8, m2-14, sd1 = 6, sd2 = 6, n2/n1 = 1.00. This sample size allows for sub-group analyses of the consult service compared to the inpatient service or other similar sub-group analysis.

For the three recruitment sites, we have approximately 1900 palliative care inpatient admissions per year and 3000 palliative care consult service admissions per year. However, many consult service admissions become inpatient admissions. Approximately a third of the total admissions per year would be both consult admissions and inpatient admissions, leaving 3280 admissions per year that reflect separate individuals. Based on eligibility rates and response rates of similar previous studies we can assume 50 % of these are eligible (*n* = 1640), ineligibility mostly due to being imminently dying. A further 33 % of those who are eligible consent to participate (*n* = 546). Of the 546 that consent, we assume that 60 % will complete data collection at Time 1 (*n* = 327). Assuming 30 % attrition at T2 (leaving *n* = 228) and 50 % attrition at T3 (since it is during bereavement, attrition may be quite high), 114 cases can be completed per year, providing the required sample size of 228 from the recruitment pool in 2 years.

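### The 97 per group was computed from a GHQ difference of 2.8, not the stated 2.4; at 2.4 (SD 6) it gives about 79% power, not 90%.

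*Protocol article*

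**What the plan says.** All the relevant statements are in the protocol article, under Sample size, power calculation and feasibility.

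- **Source of the effect.** For an earlier study of 275 family carers, the text reports that "the mean GHQ difference was 2.8 (SD = 5.6), represents a medium effect size (ES) of 0.5".
- **Planned difference.** "The sample size calculations are based on a smaller mean difference between groups of 2.4". The reason given is "as some carers in the control group will have family meetings as part of standard care".
- **Inputs listed for the calculation.** Two-sided alpha of 0.05, 90% power and "m1 = 16.8, m2-14, sd1 = 6, sd2 = 6, n2/n1 = 1.00". I read the printed m2-14 as m2 = 14.
- **Result.** 97 per group, 194 in total.
- **Feasibility paragraph.** After the expected losses to T2 and T3, it concludes that "114 cases can be completed per year, providing the required sample size of 228 from the recruitment pool in 2 years".

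**The concern.** The stated difference (2.4) and the listed means (16.8 and 14, so 2.8) cannot both describe the calculation that gave 97. The listed difference equals the undiluted figure from the earlier study, so the announced reduction does not appear to have reached the arithmetic.

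This matters because the authors raise contamination of the control group as a design issue themselves. The Standard care section accepts that some control participants will have a family meeting and says the design takes account of it. The sample size is where a reader would expect to see that. The Analyses plan also makes further sub-analyses conditional on finding no effect, so the real risk of a false negative affects how the trial will be analysed and read.

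A second inconsistency is that the section derives 194 and then describes 228 as required. The recruitment target is therefore not defined.

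**Working it through.** **Inputs.** Two-sided alpha 0.05 (z = 1.960), power 0.90 (z = 1.2816), 1:1 allocation, SD 6 in both groups, all as listed in the section. The candidate differences are 2.8 (16.8 − 14) and 2.4 (stated in the text).

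**Formula.** n per group = 2 × [(1.960 + 1.2816) × SD / d]². The squared sum of the z-values is 10.507.

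**Step 1: reproduce the plan's figure.** With d = 2.8 and SD 6: 2 × 36 / 7.84 × 10.507 = 96.5, so 97 per group. This matches exactly. Power at 97 per group is 90.1% (normal) or 89.9% (t-test).

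**Step 2: use the stated difference.** With d = 2.4 and SD 6: 2 × 36 / 5.76 × 10.507 = 131.3, so 132 per group, 264 in total. The t-test solution is 133 per group, 266 in total.

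**Step 3: power of the stated size at the stated difference.** With n = 97, d = 2.4 and SD 6, the standardised shift is (2.4/6) × √(97/2) = 2.786. Then 2.786 − 1.960 = 0.826, which gives 79.6% (normal). The t-test gives 79.2%.

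**Step 4: power with the other total.** With n = 114 per group (228/2), d = 2.4 and SD 6: (2.4/6) × √(114/2) = 3.020. Then 3.020 − 1.960 = 1.060, which gives 85.5% (normal) or 85.2% (t-test).

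**Step 5: can another reading get 97 from 2.4 at 90% power?**

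| SD | Sides | n per group |
|---|---|---|
| 6 | two | 132 |
| 6 | one | 108 |
| 5.6 | two | 115 |
| 5.6 | one | 94 |

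None gives 97. The one-sided and SD 5.6 rows also contradict the listed inputs. At 2.4, an SD of about 5.16 would be needed to make 97 sufficient, and the section gives no such value. A misprint in the means is not the explanation either: means truly 2.4 apart would have produced 132.

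All figures are for a simple two-sample comparison with no allowance for clustering.

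**The case against.** The contradiction itself is hard to contest. The fair objections concern how far it reaches.

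1. **The 228 may come from a calculation that did use 2.4.** With the earlier study's SD of 5.6, a difference of 2.4 needs 2 × 31.36 / 5.76 × 10.507 = 114.4 per group, close to 228/2, and 114 per group would then have 89.9% power. This cannot be ruled out. But the section lists SD 6, 114.4 rounds up to 115 per group (230 in total), and 228 is also simply two years of 114 completers. Even on this reading the listed inputs and the 97 would be wrong. What stands is that the allowance is missing from the inputs listed for 97; how the authors arrived at 228 is unknown.

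2. **The 79% is conditional.** It holds for 97 per group, SD 6 and a true difference of 2.4. At 2.8 the stated 90% is correct, and with SD 5.6 the power at 2.4 is about 84–85%. This is right, and the conditions should be stated. They are, however, the protocol's own planned difference, SD and group size.

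3. **Numbers at T2 may be much larger.** The feasibility chain projects 228 carers per year at T2, so 2 × 228 = 456 over two years. Split equally, 228 per group gives (2.4/6) × √(228/2) = 4.271, less 1.960 = 2.311, or about 99% power before clustering. So a shortfall is not shown for a T2 contrast if those projections hold. That does not correct the stated 97 and 194, nor settle which total is required or at which time point.

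4. **Any replacement text must not be unqualified in turn.** The Analyses plan specifies mixed models that account for clustering. This objection stands, and the wording proposed below carries the caveat.

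**Conclusion.** The concern holds. The 97 per group follows from a difference of 2.8 with SD 6. At the 2.4 the protocol says it planned for, 97 per group gives 79.2–79.6% power. The chance of missing that effect is about 20–21%, roughly double the stated 10%. Keeping both 2.4 and 90% power would need 132 per group (264 in total), which exceeds either total in the section. The 228 total reaches only about 85% at 2.4.

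These results assume SD 6, two-sided 5%, equal groups and independent observations, as the section's own calculation does. They concern the stated justification for the primary comparison; they do not show that the numbers eventually analysed at T2 would be too few. The conflict between 194 and 228 is separate and also needs resolving. Both should be corrected, because the stated power is wrong for the difference the protocol says it used.

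**What to change.** Restate the sample size paragraph on one consistent set of inputs, in one of two ways.

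- **Keep 2.4.** State that at a difference of 2.4 (SD 6, two-sided 5%), 97 per group gives 79% power and 114 per group gives 85%, that 90% would need 132 per group, and that these figures precede any allowance for clustering.
- **Keep 97 per group at 90%.** State that it rests on a difference of 2.8 and delete the claim that dilution was allowed for. This is consistent, but it leaves the sample size with no allowance for the control-group meetings that the Standard care section expects.

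In either case, give one required total, 194 or 228, and say which time point it refers to. If the other figure is only a projection of how many carers can be recruited or completed, call it that.

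The cost is wording, plus a less favourable power statement if 2.4 is kept. The correction itself requires no extra recruitment. Only a decision to hold both 2.4 and 90% power at SD 6 would raise the target, to 264 at the chosen time point.

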#### Analyses plan

The main analyses will be performed on pooled data across sites for the intervention and control groups, following an analysis of the baseline data to identify any differences between sites. We will undertake analyses as follows. Summary statistics will be calculated to compare the characteristics of carers in each group. Linear mixed models will be used to (1) compare patterns of change over time by testing the intervention group by time interaction and (2) estimating and testing differences in scores between groups at T2 and at T3 via linear contrasts, and accounting for the non-independent nature of the data in clusters. Mixed models yield unbiased estimates for data which are missing [48], and is relevant for cluster trials [49]. Sub analyses will be undertaken dependant upon obtaining a suitable sample size. In the event of ‘no intervention effect’, where possible, a sub-analysis will be conducted to compare outcomes in the control group carers who did not have a meeting (i.e. a ‘per protocol’ analysis) with those in the intervention group carers who had a meeting. In the event of ‘no intervention effect’ , a sub-analysis will be conducted on those that were moderately or highly distressed at time 1 to compare outcomes in the control group and intervention group for distressed carers. A sub analysis will also be undertaken to explore any differences in outcomes between participants recruited from the specialist palliative care in-patient facility and those recruited from a palliative care hospital consultancy service.

### Aim 2

To determine the cost-benefit and resource implications of implementing SFM meetings into routine practice.

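### The 90% power at 97 per group comes from an independent two-sample formula and is not supported for the three-site before/after design that the protocol plans

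*Protocol article*

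**What the plan says.** The section on sample size, power and feasibility describes an "Estimated sample size for two-sample comparison of means Test Ho: m1 = m2", and the resulting size "is 97 per group", 194 in total. The inputs are a two-sided alpha of 0.05, power of 90%, means of 16.8 and 14, and "sd1 = 6, sd2 = 6, n2/n1 = 1.00". The same section says: "The sample size calculations are based on a smaller mean difference between groups of 2.4". It then adds: "This sample size allows for sub-group analyses of the consult service compared to the inpatient service or other similar sub-group analysis".

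The Research design section describes something other than two independent samples. Three sites are randomised, all collect six months of baseline data, two then deliver the intervention, and one stays control throughout. Site differences are to be controlled for if that proves necessary.

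The Analyses plan pools data across sites in linear mixed models, "accounting for the non-independent nature of the data in clusters". It makes sub-analyses conditional on a suitable sample size. One of them is to "explore any differences in outcomes between participants recruited from the specialist palliative care in-patient facility" and those recruited from the consultancy service.

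**The concern.** The sample size calculation and the analysis describe different designs. The calculation treats 194 carers as independent. The analysis is to allow for carers in the same site being alike, and most control data come from an earlier phase or from a single concurrent control site. Both features enlarge the standard error of the intervention effect for a given number of carers.

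At stake is how a null result is read. The Analyses plan lets two further comparisons be triggered by a finding of no intervention effect. If that finding is taken as a null at 90% power when the real figure is lower, those comparisons start from a wrong premise. Similarly, a chance difference between the consult and inpatient settings could be presented as something the trial was sized to detect.

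**Working it through.** **1. Reproducing the plan's figure.** n per group = 2 × SD² × (1.960 + 1.282)² / d².
- d = 16.8 − 14 = 2.8, SD 6: 2 × 36 × 10.507 / 7.84 = 96.5, so 97. This matches exactly, so nothing is held in reserve for clustering, period or subgroups.
- d = 2.4, the difference named in the text: 131.3, so 132. The mismatch between 2.4 and 2.8 is a separate matter; both differences are carried below.

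**2. Inputs for the design.** From the article: 3 sites, 6 months of baseline, 2 sites switch, SD 6, N = 194, about equal control and intervention totals, 228 completers a year at T2 and 114 at T3. Assumed: equal recruitment per site-month. Equal totals then need 2T = 3 × 6 + T, so T = 18 months after baseline. At N = 194 each site has 16.17 carers before and 48.5 after, 64.67 in all. ICC (0.01, 0.05) and T1 correlation (0.6) are not in the article and are assumed.

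**3. Standard error.** Let τ² = 36 × ICC and σ² = 36 × (1 − ICC). Information on the intervention effect is the sum of two parts:
- between sites: 0.75² / [1.5 × (τ² + σ²/64.67)];
- within sites: 24.25/σ² without a period term, or 1 / [1.5 × σ² × (1/16.17 + 1/48.5)] with one.

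Fixed site effects drop the between-site part. SE = 1/√information and power = Φ(d/SE − 1.96).

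Examples:
- ICC 0: 0.674 + 0.674 = 1.347, SE 0.862, which equals 6√(2/97).
- ICC 0.01, no period: 0.412 + 0.680 = 1.092, SE 0.957.
- ICC 0.01 with period: 0.412 + 0.227 = 0.638, SE 1.252.
- Fixed site plus period: SE = 6 × √(1.5 × 0.0825) = 2.110.

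**4. Results.** Power at a difference of 2.8 / 2.4:

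| Model | SE, N = 194 | N = 194, no T1 gain | N = 194, T1 correlation 0.6 | N = 456 (T2, two years), no T1 gain | N = 228 (T3, two years), no T1 gain |
|---|---|---|---|---|---|
| Independent (plan's formula) | 0.862 | 90% / 80% | – | – | – |
| Random site, ICC 0.01, no period | 0.957 | 83% / 71% | 96% / 88% | 99% / 95% | 88% / 77% |
| Random site, ICC 0.05, no period | 1.072 | 74% / 61% | 90% / 80% | 97% / 90% | 80% / 67% |
| Random site, ICC 0.01, with period | 1.252 | 61% / 48% | 80% / 67% | 86% / 74% | 66% / 53% |
| Fixed site plus period (not stated in the protocol) | 2.110 | 26% / 21% | 38% / 30% | 53% / 41% | 30% / 23% |

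The T1 column multiplies each SE by √(1 − 0.6²) = 0.8, which lets T1 explain the same share of between-site as of within-site variance. If T1 reduces only the within-site part (σ² × 0.64 in the formulas above), the three random-site rows become 94% / 86%, 89% / 78% and 75% / 62%. All rows treat the ICC as known.

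Detectable difference at 90% power, N = 194, no T1 gain (3.24 × SE): 2.8 (independent), then 3.1, 3.5, 4.1 and 6.8 points down the table.

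**5. Subgroups, even with full independence.** Assume a 50/50 split between settings, so 48.5 carers per arm in each setting.
- Within one setting: SE = 6√(2/48.5) = 1.218; power 63% / 50%.
- Difference in effect between settings: SE = 6√(4/48.5) = 1.723; power for a 2.4-point interaction is Φ(2.4/1.723 − 1.96) = 29%.

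**The case against.** The strongest reply is that the trial may well be adequately powered. GHQ is measured at T1 and the mixed model tests a group-by-time interaction, so some gain from T1 is already built into the planned analysis. The feasibility figures imply about 456 carers at T2 over two years, not 194. With that number, ICC 0.01, no period effect and no T1 gain, power at 2.4 is 95%. The arithmetic behind 97 is also correct for its inputs. All of this stands.

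A reader might infer from the lowest row of the table that the trial has only about a quarter of the power claimed. The article does not support that. Fixed site effects together with a period term are not in the Analyses plan, and site adjustment is mentioned only as a contingency. A reader might equally infer that the design cannot reach 90% at all. That fails too: several rows reach it.

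What the reply does not do is rescue the stated figure. The article gives no ICC, no T1 correlation and no position on calendar period, and it derives the 90% from none of the things that could restore it. At T3, where 228 carers are expected, no clustered row reaches 90% without T1 gain.

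On subgroups, the Analyses plan already makes sub-analyses conditional on sample size and words the setting comparison as exploratory. The true split between settings is unknown. The loose phrase about differences in outcomes is ordinary article language, and the exact contrast may sit in an analysis plan not shown here. That part is therefore minor.

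**Conclusion.** The point holds in this form: the 90% at 97 per group is the power of an independent two-sample comparison, and the article offers no support for it under its own clustered before/after design. It does not follow that the trial is underpowered. Across the models and numbers in the table, power at 2.8 runs from 26% to 99%, and at 2.4 from 21% to 95%. The random-site models, which are closest to the Analyses plan, give 61% to 83% at 2.8 with 194 carers and no T1 gain. These ranges rest on assumed ICC, T1 correlation, equal recruitment per site-month and 6 months before with 18 after. That the answer moves from ample to poor on choices the article never states is the reason to restate it.

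The subgroup sentence is unsupported even under independence (63% / 50% within a setting, 29% for a 2.4-point interaction, with an assumed equal split), but it is a wording fault of lesser weight.

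**What to change.** Restate power and the detectable difference for the planned site-clustered before/after mixed model, including a calendar-period term. Give them over a stated range of ICC and T1–T2 correlation, and at the numbers expected at T2 and at T3, so that a reader can see which assumptions the conclusion needs.

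Minor: delete the sentence "This sample size allows for sub-group analyses of the consult service compared to the inpatient service or other similar sub-group analysis", and report the setting analysis as an exploratory group-by-setting interaction with a confidence interval.

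The cost is one calculation and some wording, with no extra recruitment. The downside is that the stated figures become less favourable.
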